## Abstract

**Background:**

Patients with psychosis frequently report difficulties getting or staying asleep (insomnia). Dissatisfaction with sleep is high. Insomnia should be treated in this group, but typically it is not even assessed. Importantly, recent evidence indicates that insomnia triggers and exacerbates delusions and hallucinations. The clinical implication is that if the insomnia is treated then the psychotic symptoms will significantly lessen. In a case series with 15 patients with persecutory delusions resistant to previous treatment this is exactly what we found: cognitive behavioural therapy for insomnia (CBT-I) led to large reductions in both the insomnia and delusions. The clear next step is a pilot randomized controlled test. The clinical aim is to test whether CBT-I can reduce both insomnia and psychotic symptoms. The trial will inform decisions for a definitive large-scale evaluation.

**Methods/design:**

We will carry out a randomized controlled trial (the Better Sleep Trial, or the BEST study) with 60 patients with distressing delusions or hallucinations in the context of a schizophrenia spectrum diagnosis. Half of the participants will be randomized to receive CBT-I, in addition to their standard treatment, for up to eight sessions over 12 weeks. The other half will continue with treatment as usual. Blind assessments will take place at 0 weeks, 12 weeks (post-treatment) and 24 weeks (follow-up). The primary outcome hypotheses are that CBT-I added to treatment as usual will improve sleep, delusions and hallucinations compared with only treatment as usual. All main analyses will be carried out at the end of the last follow-up assessments and will be based on the intention-to-treat principle. The trial is funded by the NHS National Institute for Health Research (NIHR) Research for Patient Benefit Programme. Data collection will be complete by the end of 2014.

**Discussion:**

This will be the first controlled test of CBT-I for patients with delusions and hallucinations. It will provide significant evidence for an easily administered intervention that is likely to prove very popular with patients experiencing the difficult-to-treat problems of delusions and hallucinations.

**Trial registration:**

Current Controlled Trials ISRCTN 33695128

## Background

Improvements in the treatment of delusions and hallucinations are greatly needed. One method for improving treatment involves drawing on developments in understanding these psychotic symptoms by targeting key putative causal factors one at a time (for example, [1-4]). Insomnia has been strongly implicated in the occurrence of psychotic symptoms but is yet to be a treatment target. Harvey et al. [5] explain: ‘Sleep disturbance is increasingly recognized as an important, but understudied, mechanism in the complex and multifactorial causation of the symptoms and functional disability associated with psychiatric disorders.’ Four recent studies by our group have established in cross-sectional and longitudinal designs that insomnia and paranoid delusions are linked [6-9]. For instance, in our initial study we found in a group of patients with persecutory delusions that 27% had severe clinical insomnia, 27% had clinical insomnia of moderate severity and 30% had subthreshold insomnia, that is, only 16% of patients were sleeping well. While it has long been known that sleep deprivation can bring on hallucinations [10] and that difficulties sleeping are one of the most common prodromal signs of psychotic disorders [11]. Moreover, Yang and Winkleman [12] have argued that their ‘data demonstrate that drug-free patients with chronic undifferentiated type schizophrenia suffer from profound disturbances in sleep continuity and sleep architecture.’ At a neurobiological level it has been suggested that the overactivity of dopamine D2 receptors in the striatum thought to underlie the positive symptoms of schizophrenia also enhances wakefulness [13]. The implication is that treating insomnia in patients with schizophrenia will lessen psychotic symptoms.

### Preliminary study

A large body of research, outside of psychosis groups, has found that cognitive behavioural interventions (CBT-I) are highly effective in treating insomnia [14,15]. In a recent case series, we used CBT-I with patients with psychosis for the first time [16]. Fifteen patients with persistent persecutory delusions and insomnia in the context of a psychotic disorder were individually given a standard-format, four-session CBT-I intervention. Outcome assessments were conducted at pre-treatment, post-treatment and one-month follow-up. Following the intervention, highly statistically significant reductions were found in levels of insomnia and the persecutory delusions. The effect sizes were large, and the changes were maintained at the time of the follow-up assessment. Nine patients reduced insomnia scores by at least 50% and 14 patients reduced insomnia scores by at least 25%. Five patients reduced persecutory thinking scores by at least 50% and eight patients reduced persecutory thinking by at least 25%. There were also significant reductions in levels of hallucinations, anxiety and depression. A more rigorous evaluation is required, which will test our trial procedures, and include an examination of the effects of the intervention on delusions and hallucinations.

### Pilot randomized controlled trial

A randomized controlled trial of CBT-I for patients with psychosis is now warranted. This pilot trial will: establish recruitment and follow-up rates; indicate levels of compliance with the treatment; determine whether actigraphy and sleep diaries can be used in this population; provide stronger evidence for the efficacy of the intervention (establishing treatment effect sizes); and indicate for whom the intervention is most suitable. It will test our procedures within a large mental-health unit in an NHS Trust hospital for recruitment from inpatient and outpatient services from different catchment areas. Therefore, there are three specific main aims: to establish that the trial procedures work (and fine tune where necessary), so that a Phase III trial can follow; to show that CBT-I is beneficial in improving sleep for individuals with distressing delusions or hallucinations; and to show that CBT-I has the added benefit of reducing delusions and hallucinations. The latter aims will establish treatment effect sizes. The primary outcome hypotheses are:

1. CBT-I added to treatment as usual will improve sleep in patients with psychosis compared with only treatment as usual.

2. CBT-I added to treatment as usual will reduce delusions and hallucinations compared with only treatment as usual.

The secondary hypotheses are:

1. Improvements in sleep and psychotic symptoms will be maintained over at least three months.

2. Improvement in sleep will be associated with improvements in psychotic symptoms.

3. CBT-I will lead to improvements in patient well-being and feelings of fatigue.

4. There will be indications that CBT-I is potentially cost-effective, by improving quality of life, reducing time in hospital over six months, and potentially generating NHS savings.

## Methods

### Research design

This is a prospective randomized pilot study to evaluate CBT-I in addition to standard psychiatric care versus standard psychiatric care alone in patients with distressing delusions or hallucinations (see Figure 1). A psychological intervention control group is not included in the design. We will instead examine how the treatment works by including repeated measures of insomnia and associated processes. Non-specific therapist factors will also be assessed [17]. A two-group design makes the successful completion of the trial much more feasible, while the addition of a third group would not add value in this instance. Randomization will be carried out independently by an on-line system developed by the Oxford Cognitive Health and Neuroscience Clinical Trials Unit. The randomizer programme will balance the following three variables: (i) sex (male, female), (ii) sleep problem severity (low, 15 to 21 on the Insomnia Severity Index (ISI); high, 22 to 28 on the ISI), and (iii) symptoms (hallucination only, delusions only, hallucinations and delusions). The trial therapist will inform patients of the randomization outcome, so that the research worker does not become unblinded. Rater assessments will be blind. All patients will be informed of allocation by the trial therapist to prevent the research assessors becoming unblinded. Precautionary strategies will include encouraging the therapist to consider room use and diary arrangements in the light of potential breaks of masking and reminding patients by the assessor not to talk about treatment allocation. Also, after the initial assessment, the assessor will not look at the patient’s clinical notes until the last of the ratings has been collected. The success of the blinding will be monitored; if there are breaks in the blinding, another assessor will be used from our research group. The reliability of the rater on the key interviewer measures will be formally assessed. The trial has received approval from the NHS Research Ethics Committee South Central, Oxford C (reference 12/SC/0138).

**Figure 1 F1:**
[figure not shown]
Flow diagram for the BEST study.

### Participants

Patients will be recruited from services across the Oxford Health NHS Foundation Trust, which covers a population of 1.1 million. We will seek referrals from all relevant outpatient and inpatient clinical teams who see patients with schizophrenia and related diagnoses. The inclusion criteria are: a current delusion or hallucination that has persisted for at least three months; a score of at least 2 on the distress scale of the Psychotic Symptom Rating Scales (PSYRATS) for either a delusion or hallucination [18]; a clinical diagnosis of schizophrenia, schizoaffective disorder or delusional disorder (that is, diagnosis of nonaffective psychosis (F2) in the International Classification of Diseases and Diagnostic and Statistical Manual IV); sleep difficulties lasting one month or longer with an ISI score of 15 or above (that is, above subthreshold insomnia). Participants must be aged between 18 and 65, and, where changes in medication are being made, entry to the study would not occur until at least a month after stabilization of dosage. It should be noted that we will be seeing patients when the main treatment, neuroleptic medication, has generally been tried at length and symptoms are relatively stable (persistent). It is increasingly recognized that the action of neuroleptic medication occurs rapidly [19,20]. Criteria for exclusion are: a primary diagnosis of sleep apnoea, alcohol or substance dependency; an organic syndrome or learning disability; a command of spoken English inadequate for engaging in therapy; and current individual CBT (though previous CBT experience is not an exclusion criterion). Written informed consent will be obtained from all participants.

### Planned interventions

The insomnia intervention will be provided in up to eight sessions over 12 weeks. The 12-week window will allow some flexibility for appointment times (it is quite common for patients in this group to fail to attend appointments) and the extension of intervals between the final two sessions. The exact number of sessions will depend on clinical appropriateness in the 12 week window. The main techniques, which are standard sleep interventions for CBT, are taken from four main sources [15,21-23]. The intervention is written in a manual, which we will develop further. Initially, the sessions focus upon psycho-education about sleep difficulties, assessment of the triggering and maintenance of sleep difficulties, and goal-setting. There is a checklist of factors likely to cause sleep difficulties. Based on the assessment, the active therapeutic techniques that are used included sleep hygiene, stimulus control therapy (for example, setting appropriate and regular sleep times, not doing anything else in the bed or bedroom apart from sleeping, not staying in bed if not able to sleep for longer than 20 to 30 minutes, stopping daytime naps), relaxation, and, less often, cognitive techniques to address unhelpful beliefs and attitudes about sleep, attentional bias, monitoring, and safety behaviours. The intervention is deliberately simplified, with the principal therapeutic technique being stimulus control; that is, learning to associate bed with sleep. Participants are also given written information as part of the intervention in the form of leaflets to read between sessions and on completion of the intervention. The intervention will be carried out by a qualified clinical psychologist, who carried out the case series therapy. Sessions will be taped for assessment of adherence and for competence [24]; when the purpose is clearly explained, we have found that 80% of patients with psychosis agree to recordings of sessions. We will obtain independent judgements on the quality of therapy using a random selection of therapy tapes. Patients will also be asked to assess the therapist’s empathy [25]. Standard care is delivered according to national and local service protocols and guidelines. Service use will be measured using the Client Service Receipt Inventory [26].

Secondary outcome assessments will include patient-reported outcome measures: a psychometrically validated user-led assessment (CHOICE [31]) reflecting the priorities, such as self-confidence, peace of mind and a sense of being in control, of patients with psychosis; a measure of quality of life, which includes a simple assessment of subjective general health state (EQ-5D-5 levels [32]); and a self-reported measure of well-being (the Warwick-Edinburgh Mental Well-being Scale [33]). We will also include a self-reported measure of fatigue (Multidimensional Fatigue Inventory [34]), a second self-reported measure of sleep used in many insomnia trials (the Pittsburgh Sleep Quality Index [35]), a self-reported scale of suspicious thoughts (the Green et al. Paranoid Thoughts Scale [36]), and a standard psychiatric interviewer-rated assessment (the Positive and Negative Symptom Scale [37]). We will also ask participants to complete a brief sleep diary before each assessment point, and take part in actigraph assessment (an actigraph is a watch-like device that records movement or activity and ambient light to produce an objective assessment of sleep level); this will be an important opportunity to pilot these sleep assessments with this group. We will also record service use, including medication consumption (type, dose, and time taken), use of alcohol, illicit drugs and nicotine, physical health history, adverse events, and hospital admission data (including use of the Client Service Receipt Inventory [26]). We will also, if participants are willing, collect urine for 48 hrs before each assessment, so that levels of melatonin can be tested. For an exploratory examination of mediation we will include: the Beck Anxiety Inventory [38], the Beck Depression Inventory [39], a night-time worry scale and an activity diary. To test for moderation, we will also take a mouth swab to enable DNA analysis. We will also carry out a qualitative evaluation of the patients’ experiences and preferences concerning the CBT for insomnia intervention. This will be carried out for ten of the patients using interpretative phenomenological analysis. A semi-structured interview lasting 20–30 minutes will be used, developed in consultation with our service user advisors. Interviews will be tape recorded and then transcribed before analysis.

### Assessment and follow-up

The outcome measures will be completed before randomization (0 weeks), at the end of therapy (12 weeks) and at a follow-up (24 weeks). Paper copies will be kept of all assessments and data entered into an electronic database within one day of the assessment. All the data entry for the two main outcomes will be double checked. The baseline assessment must be completed before randomization. The end of therapy assessment must be carried out after therapy has been completed. We will endeavour to have the repeat assessments carried out at exactly the timings specified, but will allow a two-week window for the post-therapy assessment and a one-month window for the follow-up assessment. As discussed, all assessments will be carried out blind to group allocation, and if a break of blind does occur then another assessor will be brought in to re-establish blindness. Participants will be paid £15 for each assessment session to compensate them for their time.

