### Statistical analysis

All main analyses will be carried out at the end of the last follow-up assessments (that is, there will be no interim analyses) and will be based on the intention-to-treat principle, with due consideration given to potential biases arising from loss to follow-up. Parameter estimates and confidence intervals of continuous outcomes will be obtained using analysis of covariance, adjusting for baseline variables. (We will also look at the effect of treatment difference by controlling for initial overall symptom severity (assessed by the Positive and Negative Symptom Scale) and medication use as a sensitivity analysis). Absolute risk difference and relative risk will be calculated for binary outcomes. Rates of attrition and loss to follow-up will be calculated for each time point. We will also assess the correlations of each measure across all time points. These findings will be used to inform the sample size for the definitive trial. For the health economic analysis, quality adjusted life-years will be used as an outcome measure, by combining EQ-5D quality-of-life information with survival data. A cost-utility analysis will be performed, in which the differences in mean costs between the CBT and standard care groups will be divided by the difference in mean outcomes between the two groups. The sample size of 60 is based on our collective recruitment experience from previous and current studies, and is considered adequate for obtaining reasonably reliable sample size estimates [40]. The patients will be recruited over 15 months. A fully detailed statistical analysis plan will be written and signed off by the investigator prior to any analysis by the trial statistician.

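### The 12-week assessment must wait for completed therapy, a condition only the CBT-I arm can face, so visit timing can differ by arm and the rule can clash with the two-week window

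*Protocol article*

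**What the plan says.** The protocol article, under Assessment and follow-up, places the outcome assessments at 0, 12 and 24 weeks. Week 0 precedes randomization, and the 12-week visit is labelled the end of therapy. The section then adds a condition: "The end of therapy assessment must be carried out after therapy has been completed". Calendar timing is worded more softly. The team will try to keep to the specified times but "will allow a two-week window for the post-therapy assessment and a one-month window for the follow-up assessment". It does not say whether the windows run before the nominal date, after it, or both.

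Planned interventions describes the therapy: "The insomnia intervention will be provided in up to eight sessions over 12 weeks". The same section explains that the 12 weeks leave room for flexible appointments because "it is quite common for patients in this group to fail to attend appointments". It also says that the number of sessions will be suited to the patient within that period. It gives no start date for the 12 weeks and does not define completion. The comparison arm receives treatment as usual and has no trial therapy.

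Under Statistical analysis, the main analyses "will be based on the intention-to-treat principle", with attention to bias from loss to follow-up.

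**The concern.** The timing of an outcome assessment should not depend on something that happens in only one arm. Here completion is mandatory while the calendar is a target, so if the two conflict the mandatory rule prevails and only CBT-I patients move. The ISI and the PSYRATS, the two key outcomes, could then be measured at different average times since randomization in the two arms.

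A second difficulty is the word 'completed'. An intention-to-treat comparison needs outcomes from all randomized patients, including those who stop attending. The sentence does not say when such a patient is due for assessment. The pilot is meant to supply follow-up rates, compliance and effect sizes for a definitive trial, so a rule that can tie follow-up to compliance blurs quantities it was set up to estimate.

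A third possibility is that waiting for completion gives the assessor a hint of allocation. This is an inference from the rule and is not stated in the article.

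**Working it through.** The article gives no figure of its own to reproduce here. The sample size of 60 rests on recruitment experience and not on a power calculation.

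**Inputs from the article.** Visits at weeks 0, 12 and 24, with week 0 before randomization; therapy within 12 weeks; a two-week window of unstated direction; 60 patients, half per arm, so 30 each.

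**Assumptions, because the article gives no values.** The delay from week 0 to the first session; visits spread evenly over the permitted days; the proportion who stop early and how much worse they do.

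**Step 1: can both rules be met?** A full 12-week course that starts L weeks after week 0 ends at week 12 + L. Take the latest reading of the window, closing at week 14. The days left for the visit are 7 × (14 − 12 − L), or none if that is negative.

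| Start delay L (weeks) | Therapy ends (week) | Days left to week 14 |
|---|---|---|
| 0 | 12 | 14 |
| 1 | 13 | 7 |
| 2 | 14 | 0 |
| 3 | 15 | none; window closed |
| 4 | 16 | none; window closed |

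The rules are incompatible once late start and overrun together exceed two weeks. If the two-week window is centred on week 12, it closes at week 13 and the limit is one week. There is no clash if the 12 weeks run from week 0 and therapy keeps to them.

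**Step 2: average timing gap when both rules can be met.** Let the window run from week a to week b. Controls are seen on average at (a + b)/2. A CBT-I patient whose therapy ends at week e, with e no earlier than a, is seen on average at (e + b)/2. The gap is (e − a)/2.

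| Window | Control mean | CBT-I mean, e = 12 | Gap | CBT-I mean, e = 13 | Gap |
|---|---|---|---|---|---|
| Weeks 10 to 14 | 12.0 | 13.0 | 1.0 | 13.5 | 1.5 |
| Weeks 11 to 13 | 12.0 | 12.5 | 0.5 | 13.0 | 1.0 |
| Weeks 12 to 14 | 13.0 | 13.0 | 0.0 | 13.5 | 0.5 |

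The gap is therefore 0 to 1 week if therapy ends at week 12 and 0.5 to 1.5 weeks if it ends at week 13. It is zero if therapy has ended before the window opens.

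**Step 3: the strict reading of 'completed'.** This applies only if patients who stop early are not assessed. The standard error of a standardized difference is √(1/n₁ + 1/n₂), which is √(1/30 + 1/30) = 0.258 with everyone assessed. If a fraction f of the CBT-I arm is left out and those patients are d SD worse than completers, the observed CBT-I mean is shifted by f × d.

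| f (assumed) | CBT-I patients assessed | Standard error | Shift for d = 0.5 to 1.0 |
|---|---|---|---|
| 10% | 27 | 0.265 | 0.05 to 0.10 SD |
| 20% | 24 | 0.274 | 0.10 to 0.20 SD |
| 30% | 21 | 0.285 | 0.15 to 0.30 SD |

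Read as 'therapy has ended', the sentence leaves nobody out and this table does not apply.

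**The case against.** The best defence is that the sentence only stops the post-therapy visit from being held while sessions are still running. The article has one visit schedule and one window for both arms. It confines therapy to 12 weeks and absorbs missed appointments by adjusting the number of sessions, so it does not plan for therapy beyond week 14. This stands in large part, and it is why the timing gap is small and can be zero. It does not remove the problem. The 12 weeks have no stated starting point, week 0 precedes randomization, and where the rules collide the wording favours completion over the calendar.

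A reader might infer that intention to treat is contradicted because patients who stop attending are never assessed. The article does not say so. It sets no minimum number of sessions, lists compliance and follow-up rates as separate pilot aims, and promises attention to loss to follow-up. What stands is that 'completed' is undefined for these patients and one plausible reading fails them.

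A reader might also infer that scheduling discloses allocation to the assessor. The article does not say who books visits or who confirms that therapy has finished. Research design has the therapist inform patients of allocation and consider diary arrangements with masking in mind, keeps the assessor out of the clinical notes, monitors blinding and replaces an assessor after a break. Replacement acts only once a break is known, so a cue remains possible, but no more than that.

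Finally, a reader might take the whole two-week window as a shift in the CBT-I arm, or put a figure on the resulting bias in the ISI effect. The window applies to both arms, and the article gives none of the inputs that such a bias estimate would need.

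**Conclusion.** The point holds as a badly fixed assessment rule, with modest and conditional consequences. A mandatory condition that can bind in one arm only is set beside a softer calendar target. The two are incompatible if a late start and overrun together exceed two weeks. Where they are compatible, the average timing gap is 0 to 1 week for therapy ending at week 12 and 0.5 to 1.5 weeks for therapy ending at week 13, given evenly spread visits.

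Selective missingness arises only under the strict reading of 'completed', and the sizes in Step 3 rest on assumed rates and differences. The masking cue is an inference. The document does not show that intention to treat is broken or that allocation is revealed. The rule is still worth changing, because it governs both key outcomes and can be repaired in a few sentences.

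**What to change.** Replace the sentence on completed therapy with: *The 12-week and 24-week assessments are due at fixed times from randomization in both arms. The same window applies to both arms, and its direction is stated. They take place whether or not therapy has been started, completed or stopped. Visits are booked from the randomization date and the assessor is not told the therapy status.* Record the number of sessions attended by the assessment date, so that incomplete exposure can be described.

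Reconcile Planned interventions with Assessment and follow-up on when the 12-week therapy period starts and how it relates to the visit. Whether therapy may run beyond that period is a clinical matter and is not settled here.

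The cost is a short change of wording. The downside is that a few CBT-I patients may be assessed with a session outstanding, which would slightly dilute the estimated effect.
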